## Introduction

Dental implants are the most widely used and reliable treatment method for individuals with fully or partially edentulous arches. The time frame for implant insertion following extraction is currently the main concern of implant therapy rather than osseointegration. Alveolar socket preservation following tooth extraction is one of the most important dental advanced skills, as numerous conditions such as traumatic extraction techniques, periodontal diseases, tumors, infections, or cysts can cause the loss of alveolar bone [1]. Alveolar ridge resorption is one of the physiological alterations that takes place following tooth extraction. After tooth extraction, alveolar ridge modeling peaks over the first 4-6 weeks, as is well known, while progressive atrophy may persist over time at a slower rate [2]. Ridge atrophy results from a substantial degree of physiologic remodeling that occurs in the alveolar socket following tooth extraction [3]. To minimize stress to the alveolus and accomplish minimal socket enlargement, atraumatic extraction must be performed. Treatment options for ridge atrophy include several forms of bone and/or soft tissue augmentation; nevertheless, these methods are known to have varying degrees of success and predictability. It is believed that socket grafting, which requires the use of grafting materials with or without barrier membranes, reduces the amount of dimensional shrinkage that occurs in the alveolar socket following tooth extraction.

For the best results, an ideal bone graft should have osteoconduction, osteoinduction, and osteoproliferation properties [4]. A range of surgical methods and biomaterials have been created to enable socket preservation. For this objective, several bone grafting methods, including synthetic and natural graft materials, have been tried. The most often used, clinically approved, or modified bone allograft material for periodontal repair is demineralized freeze-dried bone allografts (DFDBA). Bone morphogenetic proteins (BMPs) are linked to the osteoinductive capacity of DFDBA; this particular BMP combination includes BMPs 2, 4, and 7. DFDBA breaks down at a faster rate, which promotes the growth of new bone [5]. Its primary application is in the reconstruction of osseous deformities.

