Growth factors such as platelet-derived growth factor are present intracellularly and essential for the healing of wounds. Utilizing platelet concentrates has several benefits. They are crucial to regeneration. Their application has been effectively linked to bone and connective tissue repair. Platelet concentrates promote bioactivity and demonstrate nonstimulative properties. Titanium platelet-rich fibrin (T-PRF) is one of the third-generation platelet concentrates [6]. This platelet concentrate is recognized to remove the potentially harmful effect of silica, which is found in glass vacuum containers used to prepare PRF. Platelet and leukocyte cell–enriched fibrin or T-PRF is made with titanium and resembles fibrin made with the traditional PRF process. Titanium is the most corrosion-resistant metal with the highest amount of toughness. Furthermore, titanium has an amazing osseointegration quality [6]. T-PRF presents a longer resorption time and a denser fibrin structure compared to PRF, making it a promising option for the sustained release of growth factors [7].

Histologically stated, hydroxyapatite makes up the majority of the inorganic structure that makes up human enamel and dentin, which is composed of 45% organic material. Type I collagen and BMP comprise most of the organic components. An autologous dentin graft (ADG) is a viable substitute for alveolar socket preservation due to its composition of organic and inorganic components as well as its ability to promote bone formation and support bone growth [4-6]. The osteoconductive characteristics of human dentin are attributed to 4 types of calcium phosphate: amorphous calcium phosphate, tricalcium phosphate, octacalcium phosphate, and hydroxyapatite. As hydroxyapatite in dentin is primarily found as calcium phosphate with a low crystal concentration, osteoclast activity can readily break it down. Approximately 90% of its 20% organic content is composed of type I collagen network; the remaining 10% is made up of noncollagenous proteins (such as phosphoprotein, sialoprotein, osteocalcin, and osteonectin, which help calcify bone), and 10% is made up of growth factors (like insulin-like growth factor and BMPs, which give teeth their osteoinductive properties) [8]. Owing to all these properties, it can be considered as potential graft material and has been used in the past for regenerative procedures.

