### Primary Outcomes

Four months following the socket preservation procedure, the formation of new bone and changes in the alveolar socket dimensions in both groups will be assessed by radiological and histomorphometric analyses. Histomorphometric evaluations will be performed on bone core biopsies obtained at the time of implant placement at 4 months after the extraction. These samples will be processed using standard histological techniques, stained with hematoxylin and eosin, and assessed under light microscopy. Quantitative measurements such as the percentage of new bone formation, number of osteocytes, and trabecular patterns will be analyzed using Planmeca Romexis software (version 6.2.0; Planmeca Oy) to determine the measurement of bone dimensions, apico-coronal ridge height, and density in Hounsfield units.

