**Figure 2 figure2:**
[figure not shown]
Dentin grinder.

The generated root dentin particle material will be treated through 3 steps. First, the dentin cleansing solution is poured into the dish containing the particles and allowed to sit at room temperature for 5 minutes. The solution is then allowed to dehydrate using a sterile gauze. Second, the particle is then totally covered with phosphate-buffered saline, which is then put into the plate (Figure 3).

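### CBCT density in Hounsfield units sits within the primary outcomes on new bone, but the grafts differ in mineral content, so residual dentin can raise density in the ADG arm without more new bone

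*Protocol article*

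**What the plan says.** Protocol article, Methods, Primary Outcomes: at 4 months "the formation of new bone and changes in the alveolar socket dimensions in both groups will be assessed by radiological and histomorphometric analyses". The last sentence of that section takes slide-based quantities, "Quantitative measurements such as the percentage of new bone formation, number of osteocytes, and trabecular patterns", and has them analysed in the Planmeca Romexis software "to determine the measurement of bone dimensions, apico-coronal ridge height, and density in Hounsfield units".

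On the test graft, the Introduction states: "The osteoconductive characteristics of human dentin are attributed to 4 types of calcium phosphate". Hydroxyapatite is one of the four, and the same paragraph says "hydroxyapatite makes up the majority of the inorganic structure that makes up human enamel and dentin". Under Surgical Procedure for the Test Group, the roots are ground, and then: "The generated root dentin particle material will be treated through 3 steps". In the first step "the dentin cleansing solution is poured into the dish containing the particles and allowed to sit at room temperature for 5 minutes". Two washes in phosphate-buffered saline follow, and particles of 300 to 1200 microns are grafted straight away.

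On the control graft, the material is demineralised by name, and the Introduction adds: "DFDBA breaks down at a faster rate, which promotes the growth of new bone".

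Three other places bear on the point:

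- The Objective in the Abstract makes histological new bone the primary objective.
- The Introduction concedes that CBCT can show discrepancies and says histomorphometry will confirm the outcomes.
- Statistical Analysis uses an unpaired two-sided t test between groups, with P below .05 called significant.

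**The concern.** A Hounsfield reading over a healed socket sums everything radio-opaque in the region. It does not distinguish newly formed bone from graft mineral that has not yet been resorbed. If one arm receives a mineral-bearing graft and the other a demineralised one, the between-arm difference in density mixes a biological effect with a property of the material put in.

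Because density is listed under the primary outcomes, beside new bone formation, a higher value with ADG could be read as support for the hypothesis in the Abstract's Conclusions, which expects ADG to be similar or better, shown by enhanced bone formation. The same reading could arise with identical new bone in both arms.

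A second fault lies in the same sentence. It sends slide measurements, including osteocyte counts, to software whose stated outputs are ridge dimensions and Hounsfield units. As written, the measuring method for the histological endpoint is misstated.

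**Working it through.** **1. Is density offered as a reading on new bone?** The section opens with new bone formation and socket dimensions, to be assessed by radiology and histomorphometry. Its last sentence yields three radiological quantities. Two, bone dimensions and ridge height, are lengths. Density is the only one that could speak to bone formation.

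**2. Do the arms differ in graft mineral?**

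| | Test (ADG) | Control (DFDBA) |
|---|---|---|
| Mineral | calcium phosphates, including hydroxyapatite (Introduction) | demineralised by name |
| Processing described | grinding, cleanser for 5 minutes, two buffered saline washes | none beyond placement |
| Resorption | said to be easily broken down by osteoclasts; no figure | said to be faster; called fully resorbable; no figure |

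No demineralising step is described for ADG. The Discussion cites a clinical study in which demineralised dentin is named as a separate graft type, and the protocol never gives its own ADG that label. That the ADG stays mineralised is still an inference, since the composition of the cleanser is not given. T-PRF goes into both arms and offsets nothing.

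**3. Does the plan separate graft mineral from new bone?** The baseline CBCT is taken in the presurgical phase, before any graft is placed, so change from baseline does not remove graft mineral. The Introduction's remark that histomorphometry will confirm CBCT findings does not mention the mineral difference. Residual graft is not among the histological measures given as examples.

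**4. How large could it be?** The article has no figure for density. Its only calculated figure is the sample size, which supplies n. With two-sided alpha 0.01, power 0.99, SDs 0.23 and 0.24, and means 0.72 and 1.33:

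n = (2.576 + 2.326)² × (0.23² + 0.24²) / 0.61² = 24.03 × 0.1105 / 0.3721 = 7.14, rounded up to 8 per group. The stated 8 is reproduced.

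The rest is illustration with assumed inputs:

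- f: fraction of the measured region that is residual dentin, 0 to 20%.
- G: density gap between dentin and the tissue it displaces, 1000 HU.
- SD between patients: 150 or 300 HU.
- No such shift in the control arm, and no true difference in new bone.

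Shift = f × G. The unpaired t test with 8 per arm has 14 degrees of freedom and noncentrality (shift / SD) × √(8/2) = 2 × shift / SD. The chance of P below .05 (two-sided, noncentral t) is:

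| f | Shift (HU) | Noncentrality, SD 150 | Chance, SD 150 | Noncentrality, SD 300 | Chance, SD 300 |
|---|---|---|---|---|---|
| 0 | 0 | 0 | 5% | 0 | 5% |
| 5% | 50 | 0.67 | 9.5% | 0.33 | 6.1% |
| 10% | 100 | 1.33 | 23.7% | 0.67 | 9.5% |
| 20% | 200 | 2.67 | 69.9% | 1.33 | 23.7% |

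The answer is driven entirely by the residual fraction, the gap and the SD, none of which the article supplies.

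**5. The software sentence.** Earlier in the same section the cores are stained with hematoxylin and eosin and read under light microscopy. Osteocytes are counted on those slides. Ridge height and Hounsfield units come from a scan. One sentence cannot derive the second set from the first.

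**The case against.** The strongest reply is that the effect is conditional and that the plan already looks elsewhere for its answer.

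- **Residue is not established.** No passage says how much of either graft remains at 4 months, and the Introduction says osteoclasts easily break down dentin hydroxyapatite. If nothing remains, there is no bias. This stands: the article supports the direction of a possible bias but not its presence or amount.
- **The primary objective is histological.** The Objective says so, the Discussion says the study focuses mainly on histomorphometry, and Results ties the primary manuscript to the primary objective. This stands too. It confines the point to the density variable.
- **Density is not named as the measure of new bone, nor among the variables listed for testing.** This is partly right. Statistical Analysis gives only periodontal parameters, as examples. But density is listed under Primary Outcomes, in a section that assesses new bone by radiology, so a reader has no ground to treat it as merely descriptive.
- **Residual graft may be measured anyway.** The slide measures are introduced as examples, and an article condenses the full protocol. This is accepted: its absence from the list is not a defect in itself. The request is to tie it to the density result.
- **The software sentence is a drafting slip.** Probably so, and it is independent of graft mineral. It still misstates how the primary endpoint is measured and needs correcting.

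A reader might go further and infer that residual graft does make ADG look denser, by some 90 HU (0.10 × 900) to 380 HU (0.20 × 1900). The documents do not support that. Every input is assumed, the range excludes zero despite the Introduction's remark on resorption, and the formula gives both arms the same residual fraction although the control graft is said to break down faster.

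**Conclusion.** The point holds in a limited form. The between-arm comparison of CBCT density is confounded by graft mineral, in the direction the trial hypothesises, and nothing in the article removes this. Residual dentin *can* raise density in the ADG arm without more new bone; the article does not show that it *will*.

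The size cannot be computed from the article and may be small. The 5% to 70% range of spurious significance is an illustration on assumed values, not an estimate for this trial. The conclusion rests on two assumptions: that the described processing leaves the dentin mineralised, and that some of it is still present at 4 months.

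It would be wrong to infer that the primary objective is compromised. The histological percentage of new bone is not affected, and neither is the sample size arithmetic. What changes is what may be concluded from the density result. The misassigned software sentence is a separate wording error, and it holds whatever the residue.

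**What to change.** 1. Take density in Hounsfield units out of the primary outcomes. Report it descriptively by arm, as radiodensity that includes any residual graft, with no between-arm claim about bone formation.
2. Base conclusions on new bone on the histological percentage. Read the percentage of residual graft from the same sections in both arms and report it beside the new-bone percentage and the density.
3. Split the last sentence of Primary Outcomes. The CBCT software covers ridge dimensions and radiodensity; slide-based image analysis covers percentage of new bone, osteocytes and trabecular pattern.

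The cost is small: one CBCT variable loses inferential status, and there is a little more reading on slides that are already cut. No extra visit, scan or patient is needed. The change should be dated before density is compared between the arms.

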### Secondary Outcomes

After 4 months of the surgical procedure, linear phenotypic dimensional changes in the thickness of soft tissues and the midfacial and midpalatal bones at baseline and at 4 months after healing at 2 locations will be evaluated.

### Sample Size Calculation

Sample size formula was calculated using mean (SD): 
[figure not shown]
, where α=.01; β=.01; SD of newly formed bone with spontaneous healing (group 1), that is, group (δ_1_)=0.23; mean in group 1 (μ_1_)=0.72; SD of newly formed bone with ADG (group 2), that is, group (δ_2_)=0.24; mean in group 2 (μ_2_)=1.33; ratio (group 2/group 1)=1; and total samples required=8 per group. The calculation gives the result as sample required is 8 per group. The sample size was determined based on prior similar studies involving histomorphometric evaluation in socket preservation procedures. Based on the outcome variable on pocket depth with mean difference derived from previous literature [4], the sample size of 16 in total and 8 per group is adequate.

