## Methods

### Study Design

This research is a clinical trial with randomized controlled prospective parallel arms to achieve a side-by-side comparison between ADG with T-PRF and a commercially available DFDBA bone graft with T-PRF.

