### Randomization and Masking

The study group consisting of socket preservation with ADG and T-PRF or the control group consisting of DFDBA and T-PRF will be randomly assigned. Every patient will be required to complete a comprehensive medical history form, give informed consent, and receive a thorough description of the study. A secure computer system will be used for central randomization in this procedure. A distinct study code will be given to each patient, and the operators and research evaluators will receive their data in a format that maintains patient confidentiality through coding. The radiologist and the statistician will be blinded to the treatment while analyzing the data. Blind quantitative histological analysis will be performed by a trained specialist.

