### Statistical Analysis

Mean (SD) values will be found for each clinical periodontal parameter such as plaque index, papillary bleeding index, probing pocket depth, width of keratinized gingiva, clinical attachment level, and marginal bone level. Next, from baseline to 4 months, the mean data will be statistically analyzed. To equate baseline to 4-month findings for every patient, Student paired *t* test will be employed for intragroup data comparison, while the Student unpaired 2-sided *t* test will be utilized for intergroup comparison. If the *P* value exceeds .05, the observed difference will be considered nonsignificant; if it remains below .05, it will be considered significant.

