## Discussion

Socket preservation is a fundamental technique in dentistry, preserving alveolar bone structure after the extraction to facilitate optimal healing and support future dental restoration procedures. This study primarily focuses on histomorphometric analysis, which is considered a highly sensitive and accurate method for assessing new bone formation. Due to the precise and quantitative nature of histological outcomes, a smaller sample size can yield reliable and clinically meaningful data compared to studies relying solely on radiographic or clinical endpoints.

Hussain et al [4] demonstrated promising outcomes regarding the utilization of ADG in alveolar ridge preservation. Their study revealed superior dimensional stability in the study group compared to the control group, as evidenced by standardized CBCT scans. The study group's successful graft remodeling was further validated by histomorphometric analysis, demonstrating the potential of using ADG for effectively retaining the dimensional integrity of ridges. These findings highlight the need to utilize innovative biomaterials such as ADG to enhance clinical results and facilitate optimal wound healing.

Bhombe et al [5] investigated the use of PRF matrix and DFDBA as adjuvants during immediate implant placement procedures following tooth extraction. Their findings indicate that using PRFM and DFDBA in jumping gap distance as adjuvants resulted in significant coronal bone remodeling and a significant decrease in bone resorption.

In another clinical study by Elfana et al [15], histomorphometric findings demonstrated that the autogenous whole tooth and autogenous demineralized dentin graft groups exhibited higher proportions of newly formed bone (48.40%). The histology study confirmed that both types of transplants were compatible with the host tissues and showed no symptoms of inflammation.

Dwivedi et al [16] demonstrated that chair-side autogenous tooth grafts offer several advantages, including greater primary implant stability, faster recovery times, ease of preparation, reduced rates of bone resorption, and qualities that promote bone growth and socket augmentation.

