ADG, which has both osteoconductive and osteoinductive qualities, appears to be a promising alternative for alveolar ridge preservation treatments, according to a systematic study by Sánchez-Labrador et al [17]. Positive outcomes in terms of volume preservation and histomorphometric data were noted; they were reinforced by the properties of materials, such as low complication rate and cost-effectiveness in comparison to alternative bone substitutes.

Thus, the purpose of this study is to assess and compare the effectiveness of DFDBA with T-PRF and ADG with T-PRF in socket preservation by performing clinical, radiological, and histomorphometric analyses. This study plan will be reliable to prove advantages pertaining to improvements in the maintenance of vertical and horizontal socket dimensions and phenotypic dimensions.

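### The sample size is planned on dentin graft versus spontaneous healing, a contrast the trial does not make, so 8 per group is unsupported for ADG+T-PRF versus DFDBA+T-PRF

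*Protocol article*

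**What the plan says.** The protocol article, under Sample Size Calculation, plans on newly formed bone. The comparator entry reads "SD of newly formed bone with spontaneous healing (group 1", given as 0.23, with a mean of 0.72. The second planning group is ADG, without mention of T-PRF, with mean 1.33 and SD 0.24. The error rates are given as "where α=.01; β=.01", allocation is equal, and the result is 8 per group. The section ends by calling 16 patients adequate, this time on the basis of pocket depth.

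The randomised comparison is a different one. Study Design describes a "side-by-side comparison between ADG with T-PRF and a commercially available DFDBA bone graft with T-PRF", and Randomization and Masking names "the control group consisting of DFDBA and T-PRF". Every participant receives a graft plus T-PRF.

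Statistical Analysis plans a "Student unpaired 2-sided" *t* test between groups at the .05 level. The Discussion adds that, because histology is precise, "a smaller sample size can yield reliable and clinically meaningful data".

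**The concern.** A sample size calculation supports a trial only if its planning difference is one the trial could observe between its own arms. Here the 0.61 is the effect of grafting against leaving the socket to heal. The trial asks how two grafts differ. The Introduction describes DFDBA as osteoinductive and as promoting new bone, and the abstract's Conclusions hypothesise that ADG+T-PRF will be similar or better. Neither fits easily with a planned separation of 2.6 SD.

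This is the trial's only quantitative justification of size. A reader who takes beta = .01 at face value could read a non-significant result as strong evidence that the two grafts perform alike. The histological-precision argument does not fill the gap: precise measurement reduces measurement error but does not remove variation between patients.

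**Working it through.** **Inputs from Sample Size Calculation.** Means 0.72 (spontaneous healing) and 1.33 (ADG); SDs 0.23 and 0.24; alpha .01; beta .01; ratio 1. Two-sidedness and the .05 analysis level come from Statistical Analysis.

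**Step 1: reproduce the plan's figure.** Normal approximation, two-sided:

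n per group = (SD₁² + SD₂²)(z₀.₉₉₅ + z₀.₉₉)² / difference²
= (0.23² + 0.24²)(2.576 + 2.326)² / 0.61²
= 0.1105 × 24.03 / 0.3721 = 7.14, rounded up to 8.

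The stated size is reproduced. The one-sided version gives 6.43, rounded up to 7, so the plan used the two-sided formula.

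**Step 2: the effect behind it.** Pooled SD = √(0.1105/2) = 0.235. Standardised difference = 0.61/0.235 = 2.60. With 8 per group and this difference, power at alpha .01 is 99.6% by the normal approximation and 97.5% by the noncentral t. This power belongs to ADG versus spontaneous healing.

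**Step 3: match planning groups to trial arms.**

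| | Planning | Trial |
|---|---|---|
| Group 1 | Spontaneous healing | DFDBA + T-PRF |
| Group 2 | ADG | ADG + T-PRF |

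Neither planning group is a trial arm, and the comparator differs in kind. The article gives no mean or SD for DFDBA, with or without T-PRF, so no corrected sample size can be computed.

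**Step 4: what 8 per arm can detect.** Noncentral t, 14 degrees of freedom, two-sided .05: 80% power needs a difference of 1.51 SD (1.51 × 0.235 = 0.35 in planning units, 58% of 0.61). 90% power needs 1.74 SD (0.41 in planning units).

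**Step 5: illustrative power.** SD is held at 0.235, with 8 per arm. The noncentrality parameter is difference / (0.235 × √(2/8)). The fractions are assumptions.

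| True difference | Fraction of 0.61 | Power at .05 | Power at .01 |
|---|---|---|---|
| 0.458 | 75% | 95% | 80% |
| 0.305 | 50% | 68% | 39% |
| 0.203 | 33% | 36% | 15% |
| 0.153 | 25% | 23% | 8% |

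**Step 6: precision.** The 95% confidence interval half-width is 2.145 × 0.235 × √(2/8) = 0.25, about 40% of 0.61.

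**The case against.** The strongest reply is that nothing in the article shows 8 per group to be too few. That is correct. Without a DFDBA figure, a reader might infer that the adequacy claim is false, but the documents show only that it has not been demonstrated. If the grafts truly differed by 75% of 0.61, power at the planned 5% level would still be 95%; planning at alpha .01 and beta .01 left some margin. T-PRF in both arms does not by itself shrink the contrast either, because a shared additive contribution cancels.

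Three further readings go too far:

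- **The plan states 99% power.** It gives only beta = .01; the 99% is inferred.
- **A null result would be uninformative.** With a half-width of about 0.25, a result just short of significance would have an upper limit near 0.50, which excludes 0.61. Such a result would be imprecise, but it would not be empty.
- **The Discussion promises to prove ADG superior.** The sentence "This study plan will be reliable to prove advantages pertaining to improvements" goes on to socket and phenotypic dimensions. It does not concern newly formed bone and does not name ADG as the better graft, so it is not evidence on this point.

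The planning means also carry no unit, while Primary Outcomes measures new bone as a percentage. Differences in planning units may therefore not be on the scale of the trial's endpoint; the detectable differences in SD do not depend on that.

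None of this repairs the mismatch. The article states its inputs, its result and its conclusion, so this is not detail left to a fuller document.

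**Conclusion.** The concern holds in this form: the calculation is arithmetically right but uses a contrast that the trial does not make. The alpha .01/beta .01 justification and the adequacy statement are unsupported for ADG+T-PRF versus DFDBA+T-PRF, and the power for that comparison is unknown. The illustrative range at two-sided .05 runs from 95% down to 23%. It rests on assumed fractions of 0.61, on an SD of 0.235 carrying over to both trial arms, and on all 16 patients contributing data. The pocket-depth basis in the same section conflicts with the newly formed bone used in the calculation and adds no support.

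**What to change.** Keep 16 patients and the planned test. In Sample Size Calculation:

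- Replace the adequacy statement with what the design delivers: with 8 per arm and a two-sided 5% unpaired *t* test, 80% power for a difference of about 1.5 SD and 90% for about 1.74 SD.
- State that the planning data describe ADG against spontaneous healing and do not estimate the randomised contrast.
- Remove the pocket-depth basis, or correct it so that it matches newly formed bone.

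In Statistical Analysis, add that the arm difference in new bone will be reported with a 95% confidence interval, and that a non-significant result will not be read as showing similarity. In the Discussion, withdraw the sentence that justifies the small sample by histological precision. Labelling the trial exploratory is optional; an accurate statement of the detectable difference is enough.

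The cost is rewording and a less favourable stated power. No extra patients are needed.

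### The 8 per group is correctly computed, but its basis is wrong as written: two different outcomes, inputs without a unit, and an effect from a comparison the trial does not make

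*Protocol article*

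**What the plan says.** All references are to the protocol article.

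- **Sample Size Calculation, inputs.** The error rates are given by "where α=.01; β=.01". The first group is described by "SD of newly formed bone with spontaneous healing (group 1), that is, group (δ_1_)=0.23" and "mean in group 1 (μ_1_)=0.72", the second by "SD of newly formed bone with ADG (group 2), that is, group (δ_2_)=0.24" and a mean of 1.33. Allocation is 1:1, no unit is given, and the result is 8 per group.
- **Sample Size Calculation, last sentence.** The total of 16 is declared adequate "Based on the outcome variable on pocket depth with mean difference derived from previous literature".
- **Abstract, Objective.** The primary objective is histological new bone formation.
- **Primary Outcomes.** New bone and changes in socket dimensions are both listed. The histomorphometric measures open with "Quantitative measurements such as the percentage of new bone formation", followed by osteocyte number and trabecular patterns.
- **Secondary Outcomes.** Soft-tissue thickness and midfacial and midpalatal bone. Pocket depth is absent here and from the primary outcomes.
- **Statistical Analysis.** Probing pocket depth appears in the list of clinical parameters. Groups are compared by a two-sided unpaired t test; of the P value, the section says "if it remains below .05, it will be considered significant".
- **Randomization and Masking.** The arms are ADG with T-PRF and DFDBA with T-PRF.
- **Discussion.** A cited study of tooth-derived grafts is quoted with 48.40% newly formed bone.

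**The concern.** This one paragraph is the only justification for the trial's size. It names two outcomes for the same number, and gives values for only one of them. Those values are not recognisably on the scale of percentage of new bone, and they describe ungrafted sockets against ADG, whereas both trial arms receive a graft with T-PRF. The planning alpha also differs from the analysis alpha.

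What is at stake is how the result will be read. The Conclusions paragraph of the Abstract expects ADG to be similar to or better than DFDBA, and the Discussion argues that histological outcomes permit a small sample. If readers believe the trial has 99% power for its primary question, they may take a nonsignificant difference as evidence of similarity. The document does not support that level of power for the primary question.

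**Working it through.** **1. Reproduce the stated size.** Inputs from Sample Size Calculation: difference 1.33 − 0.72 = 0.61; SDs 0.23 and 0.24; alpha .01; beta .01 (power .99). Sidedness is not stated there; two-sided is taken, to match the t test in Statistical Analysis.

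n per group = (SD₁² + SD₂²)(z₁₋α/₂ + z₁₋β)² / difference²

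= (0.0529 + 0.0576)(2.576 + 2.326)² / 0.3721 = 0.1105 × 24.03 / 0.3721 = **7.14, rounded up to 8**.

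The arithmetic is right. The standardized difference behind it is 0.61 / √(0.1105/2) = 0.61 / 0.235 = 2.60. An exact t-test calculation would ask for 9, because 8 per group gives power 0.9755 at .01; this is a small difference from the normal approximation.

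**2. Which outcome?** The means and SDs are labelled newly formed bone, while the closing sentence refers to pocket depth. The document gives no mean or SD for pocket depth, so no size for that outcome can be computed or checked.

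**3. Which scale?**

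| Reading of 0.72 and 1.33 | Consequence |
|---|---|
| Proportions | 1.33 would be 133%, impossible |
| Percentages | 48.40/0.72 ≈ 67 and 48.40/1.33 ≈ 36: the values lie 67 and 36 times below the Discussion's figure |
| Some other unit | Possible, but not stated, and not percentage of new bone |

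No reading connects the inputs credibly to percentage of new bone.

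**4. Which contrast?** The 0.61 is ADG minus spontaneous healing. The trial estimates ADG+T-PRF minus DFDBA+T-PRF. The document gives no mean for DFDBA, so the size of the relevant difference is unknown.

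**5. Effect of the alpha mismatch.** With alpha .05 and everything else unchanged, including beta .01:

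0.1105 × (1.960 + 2.326)² / 0.3721 = 0.1105 × 18.37 / 0.3721 = 5.46, so 6 per group by the normal formula. By t test, 6 gives power 0.981 and 7 gives 0.993, so 7 are needed. With 8 per group at .05, power is 0.998. The mismatch is worth 1 to 2 patients per group, on the safe side.

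**6. What 8 per group can detect, whatever the unit** (two-sided unpaired t test):

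| Alpha | Difference detectable with 80% power |
|---|---|
| .05 | 1.51 SD |
| .01 | 1.94 SD |

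**7. Sensitivity, for range only.** If the true difference were half the planned one (0.305, or 1.30 SD; an assumption, not a figure in the document), power at 8 per group would be about 0.68 at .05 and 0.39 at .01.

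**The case against.** The best defence is that the number itself is correct for its inputs, and that the alpha discrepancy makes the trial larger than testing at .05 requires. Both points stand. Several stronger readings are tempting, and the document does not support them:

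- **That 8 results only from alpha .01.** It does not. The 99% power requirement matters as much: at alpha .01 and 80% power the normal formula gives 3.47, or 4 per group.
- **That readers are promised a 1% type I error and given 5%.** The .01 is a planning input; the .05 decision rule is stated openly in Statistical Analysis.
- **That the inputs cannot be percentages.** No unit is given, and 1.33% is not arithmetically impossible. The 48.40% comes from a different cited study than the one cited for the sample size, so the comparison shows implausibility, not impossibility.
- **That percentage of new bone is the single primary endpoint.** It is the first histomorphometric measure listed, among others, and socket dimensions are also primary.
- **That pocket depth cannot be measured at 4 months.** Statistical Analysis lists it among parameters compared from baseline to 4 months, and adjacent teeth are an inclusion requirement. Where it is probed is not said. The supportable point is that it is not a primary or secondary outcome.

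None of this resolves the contradiction of outcomes, the missing unit or the borrowed contrast.

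**Conclusion.** The concern holds in this form: the calculation is correct and its basis is not. The sample-size section contradicts itself on the outcome, and its inputs are not shown to belong to percentage of new bone or to the randomized comparison. The implied 99% power therefore cannot be claimed for the trial's primary question.

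The supportable statement is that 8 per group has 80% power for a difference of 1.51 SD at two-sided .05. That figure assumes an unpaired t test with equal variances, normally distributed data and all 16 patients contributing a core. The alpha inconsistency is minor and conservative for power.

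A reader might infer that the trial is too small. The document cannot establish that, because it gives neither a plausible difference nor an SD for percentage of new bone between the two arms. The finding is that the adequacy of 16 is unsupported, not that it is disproved.

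**What to change.** Rewrite the sample-size paragraph:

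1. Delete the sentence on pocket depth.
2. State the outcome, unit and source comparison of 0.72 and 1.33. If they are not percentage of new bone, or not ADG+T-PRF against DFDBA+T-PRF, say plainly that the size was not derived for the primary endpoint or the randomized contrast.
3. Use one two-sided alpha for planning and analysis: .05 as in Statistical Analysis, or .01 in both places.
4. Replace the implied 99% power with the difference detectable at 8 per group with 80% power: 1.51 SD at .05, or 1.94 SD at .01. If a credible SD for percentage of new bone is available, convert this to percentage points.

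Deleting the pocket-depth sentence and aligning alpha alone would not be enough, because the effect would still come from a comparison that the trial does not make.

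The cost is one paragraph, no extra patients and no change in conduct. The downside is a less favourable statement of power.
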